## Abstract

**Background:**

In recent years, preventive and clinical interventions for cardiovascular risk management have been implemented widely in primary care in the Netherlands. Although this has enhanced quality and outcomes of cardiovascular risk management, further improvement remains possible. In the planned observational study, we aim to examine the role of social networks of healthcare providers and patients in quality and outcomes of cardiovascular risk management.

**Methods/Design:**

In a longitudinal observational study, data on social networks of approximately 300 primary care providers from 30 general practices and 900 cardiovascular patients will be collected twice, with a six month interval, using a mix of measures. Social networks are documented with specifically designed questionnaires for patients, relatives, and healthcare professionals. For each included patient, we will extract from medical records to gather data on clinical processes and cardiovascular risk predictors. Data on self-management and psychosocial outcomes of patients will be collected using questionnaires for patients. The analysis focuses on identifying network characteristics, which are associated with (changes in) cardiovascular risk management or self-management.

**Discussion:**

This research will provide insight into the role of social networks of patients and providers in cardiovascular risk management in primary practice.

**Trial registration:**

Nederlands Trial Register NTR4069.

## Background

Cardiovascular disease (CVD) remains an important cause of mortality and reduced quality of life worldwide [1]. In 2010, CVD was the number one cause of death among women and the second cause of death for men in the Netherlands [2]. A wide range of preventive and clinical interventions targeting the population and patients at risk are recommended in prevailing practice guidelines, emphasizing comprehensive cardiovascular risk management (CVRM), life style changes, and preventive drug therapy [3]. In recent years, many conditions for providing recommended CVRM have been optimized in the Netherlands. These include the publication of a multidisciplinary clinical guideline and organizational standards for general practices, introduction of nurses in general practices, nationwide supply of paper-based and online patient education tools for CVD-patients as well as the general public, and targeted reimbursement for chronic illness care in primary care [4]. While these developments have improved CVRM, a specific number of patients still did not completely receive recommended CVRM or did not reach target values of CVRM [5]. So, the question is what additional determinants of CVRM and outcomes can be identified and addressed to optimize cardiovascular risk management.

Social network analysis (SNA) offers a new perspective on the implementation of evidence-based practice in healthcare. Previous research, which used SNA in health care, showed that social networks of patients and healthcare professionals could be measured in a valid way and showed substantial variation [6-8]. Pilot studies in primary care in the Netherlands have confirmed the feasibility and viability of specific measures for documenting social networks of information sharing [9-11]. Despite these and other studies in health care, insights into network-related mechanisms underlying healthcare delivery and self-management (health-related behaviors) are still limited. In this study, we will explore the role of social networks of healthcare providers and patients in the delivery and outcomes of CVRM in primary care. Social networks will be constructed using data on information exchange between individuals involved in CVRM.

### Theoretical background

The potential relevance of social networks for health outcomes is illustrated by a number of studies, which suggested that health-related behaviors are not randomly spread in a population but associated with social network structures [12-14]. This has led to the notion of ‘contagion processes’ in social networks, which seem to apply to a range of items, including infections, information, and behaviors. The underlying mechanisms of contagion patterns are heterogeneous, depending on the item of interest. For spread of information and behaviours, psychological mechanisms such as imitation of successful behaviours, role modelling, social comparison and selection of contacts can be drivers of contagion.

Contagion processes can be either simple or complex. In simple contagion processes, a single encounter has direct consequences. If applied to the transfer of information, the assumption is that access to information is the main enabler of uptake. Given the wide range of available information sources in health care, including many on the world wide web, and resulting information overload for both health professionals and patients, simple contagion may currently be rare. In many cases, information needs to be selected, prioritized and positively labeled to be put into action. Thus, a single exposure is often not sufficient to lead to change of knowledge or behaviors. Complex contagion represents spread of items under the influences of intensive, repeated and valued contacts. The assumptions of complex contagion are consistent with a number of theories. For instance, the Diffusion of Innovation Theory proposes that uptake of information occurs in most individuals by informal, personal contacts rather than through formal education [15].

Drawing on previous research and theories on social networks and translation of information contagion into attitudes and behaviors, several network characteristics which may influence the delivery of primary care for CVRM by health professionals and self management of patients at risk for CVD and with established CVD can be inferred. For a schematic representation of the hypothesized relations see Figure 1. For healthcare professionals we expect a number of social network characteristics to be of importance. Firstly, a high density (the proportion of all possible connections in a given network that are actually present) is expected to be beneficial as it provides multiple opportunities for various social influence mechanisms, such as for example imitation of successful behaviors and social comparison [8,16,17]. Secondly, a high frequency of contacts (within existing relationships) is expected to be important, as this enhances social influence and offers protection against egocentric choices [16,18,19]. Thirdly, high homogeneity of individuals in a network (e.g. regarding educational background) is expected to enhance social comparison uptake of information items that are disseminated in the network [20]. Fourthly, individuals with high centrality in a social network are expected to be influential as they have many connections and high centrality has been associated with enhanced knowledge transfer [21,22]. In healthcare, individuals with high centrality are expected to be present in social networks as CVRM-coordinators or case managers. Both are purposefully created to become highly central individuals in healthcare delivery networks. Fifth, an informal opinion leader may be identifiable in a network. He or she represents a person who influences opinions, attitudes, beliefs, motivations, and behaviors of others [23]. For these network-related factors, it may be noted that the direction of the social influence (e.g. better or worse CVRM) depends on the content of the information that is shared.

**Figure 1 F1:**
[figure not shown]
Hypothesized relations.

For patients we also expect network characteristics to be important for and related to self-management (that is, health behaviors for diet, physical activity, and smoking). Firstly, the presence of a high number of individuals with favorable self-management as previous research showed that self-management behaviors (e.g. smoking, alcohol use, obesity) are clustered within networks [12-14]. Secondly, the effect of having individuals with appropriate self-management within ones network should be more profound when these individuals are also connected to each other, with resulting opportunities for multiple social influence mechanisms [24]. Thirdly, networks which contain few individuals with depressive symptoms may be positively related to self-management, as depression has shown to have both a contagious pattern in networks [25] and to be related to worse health behaviors [26,27] and impaired efforts for achieving lifestyle change [20]. Fourthly, the presence of persons who can provide information on CVRM in patients’ informal networks (e.g. nurses or physicians) adds to the social capital of an individual and can be expected to enhance self-management [28].

### Research aims

The overall aims of the study are:

1. To describe social networks of health care professionals in primary care involved in CVRM as well as those of patients with established CVD or a high risk thereof using a social networks approach.

2. To explore which characteristics of social networks are linked to key aspects of the delivery of high-quality CVRM (that is, providing advice and recommended treatment) and of patients’ self-management.

3. To explore the influence of several network characteristics on changes in delivery of high-quality CVRM and in patient’s self-management.

4. To evaluate different methods for including patients in a study of social networks.

### Key hypotheses

In summary, the following key hypotheses will be explored in the planned research project:

#### Hypotheses on health professionals

Patients are more likely to receive recommended CVRM and reach CVRM targets in general practices which have social networks characterized by: high density, high frequency of contact, high homogeneity, an appointed CVRM-coordinator who has a high degree of centrality, and a consistently identified opinion leader for CVRM.

#### Hypotheses on patients

Patients are more likely to have favorable self-management and reach CVRM targets if they have social networks which contain: a high number of individuals with adequate self-management, a high number of individuals with adequate self-management who are connected to each other, few individuals with depressive symptoms, and individuals who provide access to individuals who can provide information on CVRM, particularly health professionals (such as nurses or physicians).

## Methods

### Study design

This observational research is part of the ‘Tailored Implementation for Chronic Diseases’ (TICD) project. The TICD-project has the overall aim to develop and test methods of tailoring implementation interventions to determinants of practice in chronic illness care in five different chronic conditions in five different countries in Europe [29].

This study will be performed parallel to a two-arm RCT as developed by the Dutch team (trial registration: NTR4069). This approach is chosen as it will allow for both the investigation of network characteristics for quality of current CVRM care by health professionals and self-management of patients and for associations of network characteristics with changes in quality of CVRM care and self-management after completion of the RCT intervention program. The RCT aims at enhancing primary care for CVRM by improving professional performance of practice nurses [30]. Practice nurses conduct care for patients with chronic conditions. They provide patients with education and guidance about their disease, medication-use, and changes in lifestyle and independently perform consultation hours and regular checkups.

For this RCT, comparing an intervention vs a control (postponed intervention) group, a tailored intervention package has been developed which offers practice nurses several options for enhancing their knowledge on CVRM and counseling skills. Additionally, the package provides recommendations for referral of patients. This package consists of training and feedback on motivational interviewing technique and an e-learning program on CVRM. Also, practice nurses will be advised to pay particular attention to the presence of depressive symptoms and plan action according to these as patients with CVD have a higher risk for experiencing depressive symptoms [27] with concomitant impairments in altering self-management [20]. More specifically, practice nurses are recommended to refer patients without depressive symptoms to e-health learning modules, patients with mild depressive symptoms to a physical exercise group, and patients with severe depressive symptoms to psychological help as appropriate in their practice [30]. Data on professional performance of practice nurses, patients’ self-management and treatment outcomes will be measured at baseline and follow-up at six months after the start of this intervention [30].

In the present research we will measure characteristics of social networks of health professionals and patients at the start of the intervention program and after completion of it. Social networks will be constructed on information exchange on CVRM purposes. Data on professional performance of health professionals and self management and CVRM treatment targets of patients will be collected by patients’ medical file extraction, self-report questionnaires and telephone interviews. Additionally, we will measure network characteristics of so called ‘alters’ of health professionals and patients. An alter represents an individual who has contact with the person under investigation, typically family members for patients and other healthcare providers for healthcare professionals.

### Ethical approval

The Medical Ethical Committee of Radboud University Nijmegen Medical Centre has waived approval for both the social network study and the RCT study [30].

### Sample

The sample will consist of health care professionals, patients with high risk for CVD or established CVD and their alters.

#### **
*Health care professionals*
**

We will include all health care professionals working in general practices participating in the RCT and who are involved in patient care (typically, general practitioners, practice nurses, and practice assistants). Based on power calculations in the RCT, 30 practices are planned to be included.

#### **
*Patients*
**

Eligible patients are adults aged 18 or older, with high risk of CVD or established CVD and who are capable of providing informed consent [30]. Patients with high risk for CVD have a risk score of 20% or higher of 10-years-morbidity and mortality due to CVD. International Classification of Primary care (ICPC) codes will be used to extract eligible patients from medical records. Exclusion criteria are: diabetes mellitus, pregnancy and lactation, terminal illness, cognitive impairments, and poor language skills. Per practice we plan to include 15 patients with established CVD and 15 at high risk.

#### **
*Alters*
**

*Alters of health care professionals* will comprise individuals with whom information on CVRM is exchanged but who are not part of the general practices’ network, as well as opinion leaders from outside general practices. We aim to include all alters of health care professionals.

*Alters of patients* include key individuals for information exchange, which most likely will be spouses or children of patients. We aim to include up to four persons considered to be important for dealing with patients’ condition or disease as indicated by the included patients in our measurements.

### Recruitment process and data collection

Specific details regarding the inclusion procedure of general practices and patients in the intervention are described in the protocol of the RCT [30]. For the RCT, all interventions and data collection procedures were planned to be performed from July 2013 until June 2014. The recruitment process and data collection procedures on behalf of these network studies will be performed parallel to the data collection of the RCT. Data collection procedures for social networks of health professionals and patients were planned in the same period, with some extension for patients needed until July 2014 because of our invitation procedures (see p8 for details). As data collection procedures for alters of health professionals start after receipt of completed questionnaires of health professionals and patients themselves, we expect to complete these procedures in August 2014. For a flow chart of the studies, see Figure 2.

**Figure 2 F2:**
[figure not shown]
Study flow chart.

#### **
*Health care professionals*
**

The RCT will start with an outreach visit in which a comprehensive explanation of the RCT study and network measurements on behalf of the present research will be provided to practice nurses. Outreach visits will be performed by a trained practice consultant. A practice consultant is an expert in coaching and advising general practices in processes of change and improvement. Before these practice visits, names of persons who are involved in patient care in general practices will be derived online and checked for accuracy by practice nurses and will be used to generate personalized network rosters. These network questionnaires will be handed over to practice nurses during practice visits so that she or he can spread these to other health professionals within the general practice. Health professionals within general practices typically will be general practitioners, practice nurses, and practice assistants. A letter which contains comprehensive information on the network study will be enclosed to the questionnaire. Prepaid envelopes will be provided for returning filled out questionnaires.

#### **
*Alters of healthcare professionals*
**

For including alters of health professionals, names, profession, and contact details will be extracted from completed network questionnaires of health professionals working within general practices. Invitation letters and network questionnaires will be mailed to alters within two weeks after receiving these completed questionnaires. When none or insufficient contact details are provided, we aim to collect these by using an Internet-search. Criteria entered in the Internet search will vary depending on information provided. We mainly will use Google for finding details needed.

#### **
*Patients*
**

Patients will be selected from the general practices’ electronic data base using ICPC codes during practice visits of the RCT. They will receive a questionnaire booklet at the start and end of the intervention period on behalf of the RCT [30]. For inclusion in the network study, we will include three basic network questions (see Additional file 1) in this questionnaire booklet followed by an invitation for participation in the network study. An informed consent form will be enclosed and will be returned along with the questionnaire booklet of the RCT. During the inclusion of the first six practices, patients will be randomized into one of two groups. The first group will receive an invitation in the questionnaire booklet to participate in the network study by a telephone interview. The second group will be invited by the choice to participate by 1) a telephone interview *or* 2) a paper-based questionnaire. After inclusion of these practices we will invert the design for another six practices so that the first group will receive an invitation to participate in the network study by a paper-based questionnaire and the second group will be invited by providing the choice to participate by either 1) a paper-based questionnaire or 2) a telephone interview. These response groups are included so that we will be able to compare which approach is most feasible for including patients in network measurements as current research on this is scarce. For inclusion of patients from additional practices, we will employ the inclusion method as assessed to be most feasible. The basic questions are incorporated in the RCT questionnaire to ensure that basic data for all patients is included. Questionnaires will be send and interviews will be held approximately two weeks after receipt of accepted invitations.

#### **
*Alters of patients*
**

Patients are asked to spread questionnaires to their alters, for which specific instructions will be provided in their own questionnaires or during interviews. For this purpose, patients will receive four additional questionnaires; one for their personal opinion leader (specified on network questionnaires as ‘the person considered to be most important for dealing with condition or disease’), and three for ‘important others’ (specified as ‘other persons considered to be important for handling condition or disease’) with accompanying information letters and informed consent forms. We have chosen to include four alter-questionnaires as limited current research indicates that this is the maximum number of important or significant others within patients’ networks [31]. Patients and alters can contact TICD researchers for additional questionnaires if desired.

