### Sample size calculation

The RCT study, in which the present research is embedded, is powered to detect a 15% difference in provided personalized lifestyle advice by including 900 patients clustered within 30 practices [30]. For the present research, we calculated the sample size for detecting a 15% difference in response rate of patients who are approached by 1) an invitation for participation in this study with a telephone interview) and 2) the choice for participating by a telephone interview or a paper-based test. Assuming alpha is 0.05, power of 0.80, a response rate of 50% in the first group and 65% in the second group, we estimated that we need to include 338 patients.

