In the analyses of self-management and health outcomes in patients, several multivariate logistic regression models will be estimated. For self-management, separate models will be estimated on physical activity, diet, and smoking. For health outcomes, separate models will be estimated on SBP, cholesterol, and risk score. Models will include four network characteristics as predictors: number of alters with favorable health behaviors, who are also connected among each other, number of alters with depressive symptoms, and number of alters who can provide CVRM-related information. The regression models will be controlled for trial arm (intervention vs control group), patient group (high risk or established CVD), and several personal characteristics: age, sex, ethnicity, marital status, SES, patient activation, therapy adherence, and depressive symptoms.

Two approaches will be used to investigate effects of social network characteristics on change in professional performance of practice nurses and self-management and health outcomes of patients after the intervention period at six month follow-up. First, follow-up outcomes measures will be treated as dependent variables. We will estimate similar models as described above and include baseline measures of outcomes of interest as predictors. Second, we will consider change as the difference between the baseline- and follow-up measures of the diverse outcomes of interest. Ordinal logistic regression models will be estimated, with change represented in three categories; a shift from inadequate to adequate outcomes, no change, and shift from adequate to inadequate outcomes.

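### Patient network data are collected by telephone or on paper, but the listed covariates of the patient models include neither mode nor practice block

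*Protocol article*

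**What the plan says.** All points are in the protocol article.

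- **Recruitment process and data collection, Patients.** "During the inclusion of the first six practices, patients will be randomized into one of two groups". One group is invited to a telephone interview. For the other, "The second group will be invited by the choice to participate by 1) a telephone interview" or on paper. In the next six practices the fixed option becomes paper, again against a choice of both. After that, "For inclusion of patients from additional practices, we will employ the inclusion method as assessed to be most feasible".
- **Same section, Alters of patients.** Patients pass on the alter questionnaires themselves. Their instructions come in the questionnaire or in the interview, depending on mode.
- **Statistical analyses.** The patient models use four network predictors built on alters: favourable behaviours, connections among such alters, depressive symptoms, and ability to provide CVRM information. "The regression models will be controlled for trial arm (intervention vs control group), patient group (high risk or established CVD), and several personal characteristics". The personal characteristics are then named: age, sex, ethnicity, marital status, SES, patient activation, therapy adherence and depressive symptoms. Mode, invitation group, practice and practice block are not among them.
- **Statistical analyses, first paragraph.** The invitation groups are used only to compare response rates.

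**The concern.** The mixed-mode design is deliberate and serves the fourth aim, the comparison of ways to include patients. The same design also determines how the predictors for the second and third aims are measured, and the models for those aims do not take this into account.

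There are two possible consequences. First, if one mode yields more reported alters than the other, part of the variation in the predictor is measurement artefact, and a true association is pulled towards the null. Second, if patients measured by one mode also differ in lifestyle or risk-factor control, the artefact becomes associated with the outcome and an alter count can appear to matter when it does not. The article leaves three routes open for such a difference: patients in the choice groups pick their mode, willingness to respond may depend on the mode offered, and the telephone-only and paper-only groups sit in different practices. The coefficients at risk are those that test the patient hypotheses.

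**Working it through.** **The plan's own figure.** The Sample size calculation section takes these inputs: "Assuming alpha is 0.05, power of 0.80, a response rate of 50% in the first group and 65% in the second group". The total it reports on that basis is 338 patients. With pooled variance, mean proportion 0.575 and two-sided alpha:

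n per group = [1.960·√(2·0.575·0.425) + 0.842·√(0.50·0.50 + 0.65·0.35)]² / 0.15² ≈ 169.3

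This rounds up to 170 per group (340 in total). The unpooled version gives 167 per group (334). Power at 169 per group is 0.799. The figure of 338 is reproduced. It concerns the response-rate comparison only and does not bear on the patient models.

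**How many patients fall under each procedure.** The RCT is planned "by including 900 patients clustered within 30 practices", and "Per practice we plan to include 15 patients with established CVD and 15 at high risk", so 30 per practice.

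- Practices 1–6 (telephone or choice): 6 × 30 = 180
- Practices 7–12 (paper or choice): 6 × 30 = 180
- Practices 13–30 (method judged most feasible): 18 × 30 = 540

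At the plan's assumed response rates of 50% and 65%, network participants number between 900 × 0.50 = 450 and 900 × 0.65 = 585.

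**Illustration of a spurious effect.** The article gives neither the effect of mode on alter counts nor the association of mode with outcome, so both are assumed. Set-up: mode m is split 50:50; reported count x = Poisson(2) + m·Poisson(d), so one mode adds d alters on average; logit P(adequate outcome) = g·(m − 0.5), so the true network effect is zero and exp(g) is the mode–outcome odds ratio. Each of 600 data sets per setting is fitted by logistic regression on x, with and without m. The table gives rejections at the 5% level without mode in the model.

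| N | Extra alters d | Mode–outcome OR 1 | OR 1.5 | OR 2 |
|---|---|---|---|---|
| 450 | 0.5 | 5% | 5% | 11% |
| 450 | 1.0 | 5% | 10% | 20% |
| 900 | 0.5 | 5% | 7% | 12% |
| 900 | 1.0 | 6% | 15% | 33% |

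With mode in the model, these settings give 4–6% and odds ratios per alter between 0.998 and 1.005. Without mode, the largest mean odds ratio per alter is 1.07.

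**Sensitivity to the set-up.** A narrower count (binomial, 0 to 4, mean 2.0 on paper) with N = 500 and 2,000 data sets per setting gives:

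| Adequate behaviour by mode | Extra alters | 50:50 split | 20:80 split |
|---|---|---|---|
| 55% v 45% (OR 1.49) | 0.5 / 0.8 | 8% / 16% | 7–8% |
| 60% v 40% (OR 2.25) | 0.5 / 0.8 | 20% / 40% | 11% / 21% |

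With Poisson counts and a 50:50 split, the two 60% v 40% cases fall to about 12% and 18–20%. If only a 5-point outcome gap remains after covariate adjustment, every setting tried lies between 4% and 8%.

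**Illustration of dilution.** With a true odds ratio of 1.30 per alter, no mode–outcome link and N = 900, the fitted odds ratio is about 1.25 with 0.5 extra alters and 1.21 with one. Adding mode moves these only to 1.26 and 1.23. A mode term therefore removes the spurious effect but restores little of the dilution.

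**The case against.** The strongest reply is that nothing in the article makes mode a cause of the outcome. Self-management is measured with a questionnaire, all patients receive the RCT booklet, and blood pressure, cholesterol and risk score come from the medical record. A false positive therefore needs a second link, between mode and outcome, that survives adjustment for the listed covariates, and some of these (SES, patient activation, depressive symptoms) may absorb much of what drives the choice of mode. This stands. Without that link the error rate stays near 5% and only dilution remains.

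It also stands that exposure is uneven across the predictors. Alters' depressive symptoms and connections come from the alters' own forms, and alters also report their own lifestyle. Mode reaches these mainly through which alters the patient names and reaches. The directly exposed items are the number of medically trained contacts and the patient's report of alters' behaviours. The instrument is a roster, and the article does not describe interviewers prompting for names. The three basic network questions are in the booklet for everyone.

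Three stronger readings are tempting and not supported:

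- That false-positive rates of 20 to 40% are to be expected. They need a large outcome gap between modes together with a sizeable shift in counts, and the upper end also needs an even split and a narrow count. The article gives none of these.
- That a new measurement method starts after twelve practices. The sentence concerns the inclusion method, and the one chosen may already be in use.
- That silence on the mode at six months is a defect. An article may leave that to the full protocol, and no stated model uses change in networks.

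Two replies do not remove the point. The section mentions control for potential confounders in general terms, but then names the patient covariates; the list of nurses' personal characteristics is marked as non-exhaustive and the patient list is not. The aims are exploratory, but an avoidable artefact weakens an exploratory estimate too.

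**Conclusion.** The point holds as a cheap improvement. Mode of network measurement varies by practice block, randomised invitation and patient choice, and the stated patient models do not account for it. If mode shifts patient-reported counts, true effects are diluted. If it is also related to outcome after the listed covariates, spurious effects can arise. The size cannot be derived from the article: in the illustrations it runs from about 5% false positives with no mode–outcome link, through roughly 10 to 20% under moderate assumptions, to 33–40% only at the extreme of what was tried. These figures assume a single fully exposed count and no other covariates, so they lean towards overstating the harm. They do not show that the planned models will mislead.

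**What to change.** Record the mode of network data collection for each patient. In Statistical analyses, add to the covariates of all patient models:

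- mode (telephone or paper); and
- practice, or at least practice block (first six, next six, later practices).

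Mode alone is not enough, because the telephone-only and paper-only groups lie in different practices and a lone mode term would mix the two. Add a sensitivity analysis that estimates the network coefficients by mode where numbers allow, since covariate adjustment does little against dilution.

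The cost is one degree of freedom for mode and two for a three-level block (or a practice term), plus one recorded item. If one method dominates practices 13 to 30, the smaller mode stratum may be too thin for separate models, and the sensitivity analysis should then be reported as such or omitted.
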